### RAGT

Participants will have one fitting visit/acclimatization session before the actual treatment sessions begin. Participants in the RAGT arm will receive two 50-min sessions per week. The study manualized RAGT walking protocol provides methods for progressing/tracking including a 5-min over ground walking session after RAGT to facilitate transfer of motor learning to usual walking devices [9]. The first RAGT walk will be 20 min, increasing, as able, to 45 min plus 5 min of over ground walking at the end [15]. The goal-based RAGT program uses a standardized approach to progressing body weight and guidance support and includes upper body activities while walking to encourage dual tasking and improved posture, and motor imagery practice. All robot settings and activities will be recorded in the session log.

### fPT

Participants will have two 50-min sessions per week. The manualized motor-learning based protocol forms the basis for this intervention. Its focus is on balance (a key issue for children with cerebral palsy that cannot be addressed in the fully supportive RAGT device) and multi-plane gait-based motor skills. Each weekly fPT session will consist of 50 min of active treatment, a ‘dose’ equivalent to time spent in active treatment in the RAGT arm. The treatment program is menu-based. The physical therapist will choose areas that best link with the child’s goals and abilities [34] and document these in the session log. Techniques that focus exclusively on body structure changes will be not be permitted (e.g., inhibitive casting, kinesiotaping, functional electrical stimulation).

### RAGT + fPT group protocol

Participants will alternate between RAGT and fPT sessions for the duration of the 8 to 10 week intervention phase. Sessions will consist of two sessions of RAGT 1 week alternating with two sessions of fPT the following week. RAGT will always commence in week 1. The fPT will build on motor learning principles because the activities will allow the child to practice motor skills in a variety of different activities. The fPT sessions will augment and build on the previous week’s RAGT work, and set the stage for the following week’s RAGT sessions. Techniques focusing on body function/structure changes will be prohibited.

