There have only been a few studies evaluating the effectiveness of RAGT with children and youth with cerebral palsy. Initial research was conducted with ambulatory individuals aged 4 to 20 years with cerebral palsy. In these small sample, one-group, pre-post intervention studies [16–20] participants showed improvements in gross motor skills (as measured by the Gross Motor Function Measure [GMFM] [21]), gait velocity and endurance [16, 22], and gains were maintained for 6 months [18]. Participants improved equally on the GMFM Stand and Walk Dimensions (i.e., mean gains about 5 points in each after 12 sessions given over 3 weeks), suggesting an added effect on postural stability for standing skills [20]. Appreciable changes in motor performance were achieved after participation in a short but highly intensive Lokomat® program (i.e., 3 to 4 weeks, total of 12 to 16 sessions) [20, 22]. GMFM Walk Dimension improvement was linked with total distance and time walked on the Lokomat® (*r* = -0.75, *p* < 0.001), [20] suggesting a dose dependency. However the lack of a control group in these studies precludes firm conclusions about the efficacy of RAGT. A recent small RCT with 52 children with cerebral palsy (GMFCS II/III) demonstrated no advantage of RAGT over a physical therapy program for walking speed or range of motion [23], however the authors cautioned against making firm conclusions due to several study limitations. Research in this area is generally comprised of studies that are methodologically weak (i.e., one group pre-post test designs, small sample sizes that limit statistical power and often lack clear descriptions of therapy protocols) [9]. Outcome measurement is often limited to the GMFM, which, provides information on foundational motor skills, but does not measure impacts on functional abilities and participation.

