### Methods/Design

This trial is a concurrent, mixed methods study [25]. Specifically, the quantitative arm is a multi-centre RCT with four groups (2^2^ factorial design, i.e., RAGT absent/present, fPT absent/present) with two periods of post-intervention assessments (immediate and 3 months later) (See Fig. 1 for Consort flow diagram). The RCT is linked with an interpretive descriptive [26] qualitative study arm. Methods for the quantitative and qualitative components are described separately.

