### Treatment

There are three intervention groups: 1) RAGT, 2) RAGT + fPT, 3) fPT, and 4) one maintenance therapy control (CONT) arm. All three intervention groups will receive two 50-min sessions per week, separated by 2 or 3 days conducted over 8–10 weeks. This protocol meets the minimum recommended duration of 60 days for intensive interventions (as determined in a meta-analysis of PT treatments in cerebral palsy) [31]. In addition, 3 sessions per week may be very challenging for families and therefore the planned intensity and duration is also based on clinical feasibility.

The LOK and fPT sessions are built on current motor learning theory principles [32] and scoring of extent of their use (treatment fidelity) will be possible via use of the Motor Learning Strategy Rating Scale (MLSRI-20) [33] by an external PT assessor with videos from two sessions per child (4^th^ and 8^th^ sessions) [32]. The prompt scoring of the session video and review by the centre investigator will permit prompt feedback to the treating PT if motor learning strategy use levels do not reach the targeted minimum score of 40 %.

Children in all four groups may continue to participate in ‘maintenance therapy’ (commonly done by children with cerebral palsy between blocks of active therapy) if they are doing so prior to the study. This may include range of motion/stretching and basic isometric strength home program as well as up to 10 min per day of exercise bicycle **or** treadmill **or** general walking practice. Families will be asked to discontinue other active therapy during the trial.

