### Statistical analysis

Data will be described (e.g., means, standard deviations, frequencies) for each intervention group and each stratification variable. Graphical summaries will include mean plots and boxplots. Change scores (post minus pre, follow-up minus post) will be summarized for each outcome. For each change score and outcome, an ANOVA for the two-factor factorial design will test the effect of each factor (RAGT, fPT) and their interaction (RAGT*fPT) on mean change score. Confidence intervals (95 % CIs) will be reported for the mean of each intervention group. Further, mixed-effects multiple linear regression models will be developed for each outcome with centre as a random effect, centre by intervention as an interaction (to assess centre effect), and other important variables (e.g., age and GMFCS level) as covariates. Variables will be dropped from the model one at a time if *p* > 0.05, and residual diagnostics will assess model fit. This modeling will allow us to assess the effect of the interventions in the presence of important variables that were not balanced across intervention groups by randomization and also can easily deal with incomplete observation times. All main analyses will be based on intent-to-treat with secondary analyses of those with >80 % adherence to their intervention. R [52] will be used for statistical analysis by a data analyst blinded to intervention group.

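### The combined arm gives about half of each therapy, so the absent/present factorial tests do not estimate full-course effects, the interaction is confounded with dose, and the 85% power applies to marginal effects only

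*Protocol article*

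**What the plan says.** Methods/Design defines a 2×2 factorial with factors "RAGT absent/present, fPT absent/present". The Treatment section sets one total for every active arm: "All three intervention groups will receive two 50-min sessions per week, separated by 2 or 3 days conducted over 8–10 weeks". Each single-therapy arm spends all of that time on its own therapy (RAGT: "Participants in the RAGT arm will receive two 50-min sessions per week"; fPT: "Participants will have two 50-min sessions per week"). The combined arm starts with a week of RAGT, "alternating with two sessions of fPT the following week", and continues alternating.

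Sample size claims 85% power, at a type I error of 0.05 and 36 per group, for an effect size of 0.25 on RAGT, on fPT and on their interaction. With SD 10, it equates this to an SD among means of 2.5. Statistical analysis tests each factor and "their interaction (RAGT*fPT) on mean change score". Research question i compares RAGT with functional therapy. Question ii asks whether the combination beats either therapy alone. On dose, the Background notes that GMFM Walk gain was linked to total distance and time on the device, "suggesting a dose dependency".

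**The concern.** A factorial main effect has a simple meaning when the factor is the same thing in both of its cells. Here, RAGT present is a full course in one cell and about half a course in the other, where fPT has replaced the remaining sessions. The combined arm substitutes one therapy for part of the other; it does not add one to the other.

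Three things are at stake:

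- A RAGT or fPT main effect could be read as the benefit of the full course given in the single-therapy arm, which it does not estimate.
- The interaction could be read as synergy or antagonism when part of it may come only from fewer sessions of each therapy.
- The 85% could be taken as the power to detect a 5-point benefit of a full course.

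**Working it through.** **Sessions.** Two per week, alternating weekly, RAGT first:

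| Weeks | Each single-therapy arm | Combined: RAGT | Combined: fPT |
|---|---|---|---|
| 8 | 16 | 8 | 8 |
| 9 | 18 | 10 | 8 |
| 10 | 20 | 10 | 10 |

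**The plan's own figure.** From Sample size: 36 per group (N = 144), alpha 0.05, f = 0.25. The noncentrality is λ = N·f² = 144 × 0.0625 = 9. The noncentral F with 1 and 140 df gives power 84.6%, so 85% reproduces. An SD among two marginal means of 2.5 is a 5-point difference between those means.

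**Cell means.** Let a full course add R (RAGT) or F (fPT) over control. Let half a course keep a fraction q of that, with no synergy. The value of q is an assumption, since the protocol gives none. The means are control 0, RAGT R, fPT F and combined q(R + F). Then:

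- RAGT main effect = [R + q(R + F) − F]/2
- interaction contrast = q(R + F) − R − F = (q − 1)(R + F)

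**R = F = 5, SD 10.** The main effect is 5q, f = 5q/20 and λ = 144f².

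| q | Main effect | λ | Main-effect power | Interaction contrast |
|---|---|---|---|---|
| 0.5 | 2.5 | 2.25 | 31.9% | −5 |
| 0.75 | 3.75 | 5.06 | 60.8% | −2.5 |
| 0.9 | 4.5 | 7.29 | 76.5% | −1 |
| 1 | 5 | 9 | 84.6% | 0 |

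**Unequal therapies.** With R = 5, F = 0 and q = 0.5, the RAGT main effect is (5 + 2.5 − 0)/2 = 3.75. The fPT main effect is (0 + 2.5 − 5)/2 = −1.25, so an inert therapy appears harmful because it displaced RAGT sessions.

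**Synergy hidden by dose.** With R = F = 5 and q = 0.5, a true synergy of 5 points raises the combined mean from 5 to 10. The main effects return to 5 and the interaction is 10 − 5 − 5 = 0. A zero interaction is therefore compatible with real synergy, just as a negative one is compatible with no antagonism.

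**Research questions.** Question i is R − F. This equals the difference between the two main effects, but none of the three planned F tests tests it. Question ii is combined − R and combined − F, and the interaction is neither.

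**Power of a pairwise contrast**, 36 v 36, pooled error with 140 df, λ = 18(δ/SD)². At SD 10, δ = 5 gives λ = 4.5 and power 55.8%; δ = 3, the plan's clinically important difference, gives λ = 1.62 and power 24.4%. Neither allows for multiplicity.

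**The case against.** **The 85% is not an error.** Sample size describes factorial F tests and an SD among means, which is the language of marginal effects, and the figure reproduces for those. A reader might infer that the stated power is wrong. The documents do not support that, because they never say that 5 points is the effect of a full course against control. This stands. The lower figures need both that reading and q below 1.

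**No dose-response is given.** A reader might infer that a negative interaction is built into the design. It is negative only if half a course loses benefit and synergy does not make up for it. The Background's dose remark concerns RAGT only and rests on uncontrolled studies that the protocol itself treats with caution. Nothing comparable is given for fPT. The combined-arm section also expects fPT to build on the preceding RAGT work, so synergy is part of the rationale. This stands too, and is why q is shown as a range.

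**Equal therapy time is a legitimate choice.** It keeps total time from confounding comparisons among the active arms, and the Treatment section links the intensity to feasibility for families. Agreed: the fault lies in attaching absent/present power and interpretation to that design, not in the design.

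**Cell means will be visible, and an SAP may add contrasts.** The plan reports a 95% CI for each group's mean. However, the protocol text itself fixes the three factorial tests as the inferential analysis and sizes the trial on them, so this is not merely a detail left to another document.

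**Conclusion.** The concern holds in a limited form. From the protocol's own schedule, each therapy is given for about half as many sessions in the combined arm as in its single-therapy arm. Whatever q is, the planned interaction cannot separate synergy or antagonism from dose, and the three tests do not directly address questions i and ii. The main effects equal full-course effects only in special cases, such as q = 1 without synergy.

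The numerical loss is conditional. If 5 points is the full-course effect of each therapy at SD 10, with no synergy, main-effect power runs from about 32% (q = 0.5) to 85% (q = 1), and the expected interaction contrast from −5 to 0 points. The protocol does not say where in that range the trial lies. The 85% remains correct for marginal effects of f = 0.25.

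**What to change.** Leave arms and schedule unchanged.

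1. **Statistical analysis.** Make contrasts of the four arm means the key analysis: RAGT v fPT (question i); combined v RAGT and combined v fPT (question ii); and each single therapy v control. State that the factorial main effects and interaction are secondary, and must not be read as full-course effects or as synergy or antagonism.
2. **Methods/Design.** Say that the combined arm has the same total therapy time as the single-therapy arms, so that factor presence does not mean the same number of sessions in each cell.
3. **Sample size.** Say that 85% applies to marginal effects of f = 0.25, and give power for the pairwise contrasts: about 56% for 5 points and 24% for 3 points at SD 10 with 36 per arm, before any multiplicity adjustment.

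Replacing the interaction by combined minus the average of the two single arms would not solve the problem. With R = F = 5 and no synergy, that contrast is 10q − 5. It is zero only at q = 0.5, and is +2.5 at 0.75 and +5 at 1. It also does not show whether the combination beats the better single therapy.

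The contrasts come from the same four arm means and need no new data. The cost is a less favourable stated power.

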### Monitoring co-interventions

Maintenance therapies such as home stretching and strengthening routines can be continued for all four groups throughout the study because these therapies have questionable efficacy [35–37] and will likely be equally used across all four groups as they are common PT recommendations. Mobility-based active therapy must be discontinued ≥ 2 weeks prior to baseline assessment. Throughout the 8–10 week intervention period and the 3-month follow-up period, parents of children in all four groups will be asked to report about other therapies received or physical activities participated in during the week. Use of other gross motor interventions will also be tracked by the treating physical therapists.

### Outcomes

All study outcomes will be measured pre-/post-intervention (< 10 days pre-intervention and post-completion), and at 3 m follow-up (+/- 10 day window). Trained pediatric physical therapists with pediatric experience will be trained to conduct the assessments. Assessors will be assigned to a child. While inter-rater reliability of all of the selected measures is good to excellent, use of the same assessor will support a smaller minimum detectable change. This sensitivity is particularly important since the sample size was based upon a small (but clinically important) effect size. Prior assessment data will not be available to the assessor at the follow-up assessments. Assessments will be video-recorded and a random sample of 20 % of the assessment’s video-recordings will be scored by an independent assessor who will not be aware of assessment sequence order. This double scoring will be done through the study to flag any scoring issues and allow remedial action.

#### Primary outcome

The primary outcome measure is the GMFM-66 [21]. It has strong validity and responsiveness with children with cerebral palsy and has been used in prior RAGT studies. The GMFM-66 evaluation will be limited to Dimensions D (Stand) and E (Walk/Run/Jump).

#### Secondary outcomes

Secondary outcomes include higher level gross motor functioning (the Challenge Module) [38] for children in GMFCS level II, walking capacity [39, 40], gait quality [41] individualized goal attainment scores [42, 43], balance [44, 45], quality of movement [46], functional abilities [47], physical activity levels, self-efficacy for physical activity [48], participation (PEM-CY) [49], and quality of life [50, 51]. A list of included outcomes and associated measures are included in Table 1.

**Table 1 Tab1:** Outcome measures

Outcome	Outcome measures
Gross motor abilities	GMFM-66 (Dimensions D- Stand & E – Walk/Run/Jump) [21] Challenge Measure (GMFCS level II) [38] and GMFM Dimensions D and E with aids and orthoses (GMFCS III) [21]
Walking capacity/gait	1- [39] and 6-Minute Walk Test [40], Bloorview Barefoot Gait Assessment (scored from video) [41]
Individualized goal attainment	Canadian Occupational Performance Measure (COPM) [42] and Goal Attainment Scale (GAS) [43]
Standing and Walking Balance	Pediatric Balance Scale [44], Quality FM (Stability from GMFM-66 video) [46], Activities Balance Confidence Scale [45]
Functional abilities	PEDI-CAT [47]
Physical Activity levels	Accelerometry (5 days)
Physical Activity Self-efficacy	Self-Efficacy for Physical Activity [48]
Participation	Participation and Environment Measure for Children and Youth (PEM‐CY) [49]
Quality of life	KidScreen [50] and Students’ Life Satisfaction Scale (SLSS) [51]

### Statistical analysis

Data will be described (e.g., means, standard deviations, frequencies) for each intervention group and each stratification variable. Graphical summaries will include mean plots and boxplots. Change scores (post minus pre, follow-up minus post) will be summarized for each outcome. For each change score and outcome, an ANOVA for the two-factor factorial design will test the effect of each factor (RAGT, fPT) and their interaction (RAGT*fPT) on mean change score. Confidence intervals (95 % CIs) will be reported for the mean of each intervention group. Further, mixed-effects multiple linear regression models will be developed for each outcome with centre as a random effect, centre by intervention as an interaction (to assess centre effect), and other important variables (e.g., age and GMFCS level) as covariates. Variables will be dropped from the model one at a time if *p* > 0.05, and residual diagnostics will assess model fit. This modeling will allow us to assess the effect of the interventions in the presence of important variables that were not balanced across intervention groups by randomization and also can easily deal with incomplete observation times. All main analyses will be based on intent-to-treat with secondary analyses of those with >80 % adherence to their intervention. R [52] will be used for statistical analysis by a data analyst blinded to intervention group.

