### Research questions

i)What is the comparative effectiveness of RAGT and a functional therapy program for improving gait-related motor skills of ambulatory children and youth with cerebral palsy?ii)Does combining RAGT and functional therapy result in greater improvements in gait-related skills of ambulatory children and youth with cerebral palsy than RAGT or functional therapy alone?iii)What are families’ experiences with the interventions and perceptions of outcomes, and what are the associated implications for interpretation of the RCT results and use of RAGT and functional therapy?

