### Sample size

The sample size of 144 children represents 9 children per age group (<13y; 13 to 18y), GMFCS strata, and intervention combination. An additional 16 participants will be recruited to accommodate an estimated 10 % drop out rate (144/.9) for a total of 160. The 10 % drop out rate was based on the current 7 % drop out rate in the feasibility trial conducted at Holland Bloorview. Sample size calculations were based on pre- to post-intervention change on the primary outcome (Gross Motor Function Measure-66) (GMFM-66) [21] and a two-factor factorial design (F tests). For the GMFM-66 change score, assuming a Type I Error of 0.05 and 36 patients per group, the study will have 85 % power to detect an effect size of 0.25 for the RAGT group, 0.25 for the fPT group, and 0.25 for the interaction. Assuming a standard deviation (SD) of subjects of 10, these effect sizes correspond to an actual SD among appropriate means of 2.5. For the GMFM-66, Dimensions D and E, mean change scores of 5.3 (SD = 5.6) and 5.9 (SD = 7.1) have been reported after Lokomat® training [20] and 4.6 (SD = 7.1) for PT [27]. These numbers correspond to effect sizes of 0.9 (GMFM Dimension D), 0.8 (GMFM Dimension E) for the Lokomat®, and 0.6 (GMFM-66 score) for PT. However, a change of 3 points on the GMFM-66 is considered a clinically important difference [28]. Thus we have amplified our power to detect a small effect size (0.25) among groups. PASS [29] was used to calculate sample size. Recruitment will take place at the three sites Holland Bloorview (Toronto, Canada), Glenrose Rehabilitation Hospital (Edmonton, Canada) and the Rehabilitation Institute of Chicago (Chicago, U.S.) over a period of 4 years.

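### The stated factorial tests contain no RAGT-versus-fPT contrast, answer combined-versus-single only if there is no interaction, and the 85% power does not carry over to these comparisons

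*Protocol article*

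**What the plan says.** Under Research questions, the protocol article asks (i) "What is the comparative effectiveness of RAGT and a functional therapy program for improving gait-related motor skills" and (ii) "Does combining RAGT and functional therapy result in greater improvements in gait-related skills" than either therapy given alone. The abstract describes the aim as the relative effectiveness of the three active conditions, and the Discussion calls it critical to know whether RAGT benefits children more than over-ground training.

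Under Methods/Design, the trial is a two-by-two factorial ("RAGT absent/present, fPT absent/present"). The Statistical analysis section says that, for each change score, "an ANOVA for the two-factor factorial design will test the effect of each factor (RAGT, fPT) and their interaction (RAGT*fPT". The 95% intervals it promises "will be reported for the mean of each intervention group". It then adds mixed-effects regressions with centre, centre by intervention, and covariates. It does not say how treatment is coded in those models, and it names no contrast between arms.

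The Sample size section, "assuming a Type I Error of 0.05 and 36 patients per group", claims "85 % power to detect an effect size of 0.25 for the RAGT group, 0.25 for the fPT group, and 0.25 for the interaction".

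**The concern.** Both quantitative questions compare active arms with one another. The planned tests compare RAGT present with RAGT absent, compare fPT present with fPT absent, and test for departure from additivity. These are different quantities.

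If the analysis is run only as stated, the report on the headline comparison would hold two main-effect p-values, an interaction p-value and four arm means with intervals. One significant and one non-significant main effect is not a test of one therapy against the other. A reader could also take the 85% figure as the power for the head-to-head question, and it is not.

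**Working it through.** **Inputs.** From Sample size: 36 per arm (144 in total), two-sided 0.05, effect size f = 0.25, SD 10, SD among means 2.5, and a 3-point change on the GMFM-66 described as clinically important. The same section cites change-score SDs of 5.6 and 7.1 from earlier studies. From Treatment and the combined-group protocol: all active arms get two sessions a week, and the combined arm alternates RAGT weeks with fPT weeks. Write the four arm means as C (control), R (RAGT), F (fPT) and RF (combined).

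**Step 1: the plan's own figure.** The noncentrality is λ = f² × N = 0.0625 × 144 = 9. With 1 and 140 df at 0.05, power is 0.846, so the stated 85% reproduces. For a main effect (72 versus 72), f = 0.25 is a difference of 2 × 2.5 = 5 points. For the interaction RF − R − F + C, it is 4 × 2.5 = 10 points.

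**Step 2: what the planned tests estimate.**
- RAGT main effect = (R + RF − C − F)/2
- fPT main effect = (F + RF − C − R)/2
- Interaction = RF − R − F + C

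**Step 3: what the questions need.**
- Question (i): R − F = RAGT main effect − fPT main effect. This difference can be estimated, but no test or interval for it is planned. The gap exists even under exact additivity.
- Question (ii): RF − R = fPT main effect + interaction/2, and RF − F = RAGT main effect + interaction/2. The main effects equal these contrasts only when the interaction is zero.

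**Step 4: why the significance pattern does not stand in for question (i).** Assume each therapy adds 5 points and the effects are additive (means 0, 5, 5, 10). Then R − F = 0, and each main effect has power 0.846. The two tests are close to independent in a balanced design, so the chance that exactly one is significant is about 2 × 0.846 × 0.154 = 0.26. About one such trial in four would look as if one therapy worked and the other did not.

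**Step 5: why additivity matters for question (ii).** The combined arm receives about half the sessions of each therapy that a single-therapy arm receives. Assume each active arm gains 5 points over control (means 0, 5, 5, 5). All three question contrasts are then 0, yet both main effects are 2.5 and the interaction is −5. At SD 10 each of the three planned tests has power 0.32. A significant main effect could be misread as a benefit of adding the second therapy, and the interaction test would usually miss the non-additivity.

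**Step 6: power for the pairwise contrasts.** The standard error is SD × √(2/36) and λ = d²/(2 × SD²/36), with 140 error df. At SD 10, d = 5 gives λ = 25/5.556 = 4.5, half the value in Step 1, and d = 3 gives λ = 9/5.556 = 1.62.

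| SD | Power at 5 points | Power at 3 points |
|---|---|---|
| 10 (design assumption) | 0.558 | 0.244 |
| 7.1 | 0.843 | 0.429 |
| 5.6 | 0.964 | 0.617 |

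These figures are unadjusted. At SD 10 the difference detectable with 85% power is about 7.1 points, and the 95% CI half-width for a pairwise difference is about 4.7 points. With Bonferroni over three contrasts at SD 10, power is 0.38 at 5 points and 0.13 at 3 points.

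**The case against.** The strongest reply has four parts.

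1. Under additivity the main effects are the combined-versus-single contrasts, with the full 72-versus-72 precision, and the plan also tests the interaction. This stands. A reader might infer that the plan answers neither question, but for question (ii) the correct statement is conditional on no interaction. The condition has weight because the interaction test has limited power (Step 5) and the protocol itself treats interaction as possible by testing and powering it.

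2. The information is not lost. The arms are independent and their means, SDs and intervals will be reported, so the differences and approximate intervals can be derived. The mixed model might also deliver arm-versus-arm coefficients, depending on a coding that is not stated. A reader might therefore infer too much from saying that the trial will yield no estimate for its questions. What the document lacks is a named analysis.

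3. An article condenses its protocol, and named contrasts or a multiplicity rule may sit in an analysis plan that is not shown. This stands for the multiplicity rule, whose absence is not criticised here. It does not dispose of the main point: the article does state its tests, its intervals and its power basis, and these do not line up with its own questions.

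4. SD 10 may be pessimistic, since the cited change-score SDs are lower, and the 3-point figure is given for a change and not clearly as a between-arm margin. Both stand, which is why the range of SDs is shown and 3 points serves only as a reference value.

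**Conclusion.** The mismatch is real. No named analysis answers question (i), and question (ii) is answered only if the interaction is zero, which the design of the combined arm gives no reason to presume. The 85% power is correct for what it describes, namely both main effects and the interaction. It does not describe the pairwise comparisons. Those have about 56% power at 5 points and 24% at 3 points at SD 10, rising to 96% and 62% at SD 5.6. These figures assume 36 analysable children per arm, a common SD, two-sided 0.05 and no multiplicity adjustment. The group means in Steps 4 and 5 are illustrations, not forecasts.

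A reader might go further and conclude that the factorial analysis is wrong, that the arm-mean intervals should go, or that the trial must enrol more children. The documents do not support that. The factorial tests and arm-mean intervals are legitimate, and the missing contrasts come from the same four-arm model.

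**What to change.** For the primary outcome, prespecify three contrasts from the same four-arm model: RAGT minus fPT for question (i), and combined minus RAGT and combined minus fPT for question (ii). Give each a 95% CI for the difference, and report them beside the factorial tests and the arm-mean intervals. State the pairwise power or expected precision next to the factorial power.

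No new data, arm, assessment or enrolment is required; the change is one of wording and reporting. The cost is candour about power. The figure attached to the headline questions falls below 85% at SD 10, and falls further if a multiplicity adjustment is applied (about 38% at 5 points and 13% at 3 points with Bonferroni over the three contrasts).
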